#### Secondary outcome measures

Further feasibility outcomes are as follows:1. Acceptability of the intervention assessed with Likert ratings 0–5 on dimensions of readability, clarity, effort, enjoyment, concentration, helpfulness, and progress regarding therapy materials at 2-week post-intervention and qualitative interviews within 1-month post-intervention.2. Acceptability and suitability of outcome measures assessed with a Likert scale at 6 months, qualitative interviews, and % willing to complete the measures at each timepoint (i.e., baseline, within two weeks after the intervention, 3- and 6-month follow-ups). The acceptability rating scale for the outcome measures will cover overall acceptability, acceptability of the nature of the questions asked in the measures, the time it took to complete the measures, and the number of times they were asked to complete the measures.3. Adherence to the intervention (% of activities accomplished) by the end of the study. This will be determined from the number of items completed on the adherence checklists completed by the facilitators after each session.

In terms of criteria required for progression to a trial, we will establish the feasibility of our study design and intervention using a red-amber-green light system (or otherwise named stop-amend-go). We will use the percentages gained from recruitment, retention, adherence, and acceptability measures and establish feasibility using the following progression criteria:

Definite go (‘green light’) defined as follows: ≥ 60% of eligible participants consent to feasibility trial. ≥ 70% retention of consented participants in both arms of the trial at 3- and 6-month follow-up. ≥ 90% of at least one primary outcome measure is completed, including 6-month follow-up. > 75% of all activities in intervention will be undertaken. > 75% of participants who complete the intervention will agree that the overall intervention is acceptable.

*Amber — for further discussion and modification* as follows:40–59% of eligible participants consent to feasibility trial.50–69% retention of consented participants in both arms of the trial at 3- and 6-month follow-up.70–89% of at least one primary outcome measure completed.60–75% of all activities in intervention will be undertaken.60–75% of participants who complete the intervention will agree that the overall intervention is acceptable.

Definite stop (‘red light’) defined as follows: < 40% of eligible participants consent to feasibility trial. < 50% retention of consented participants in both arms of the trial at 3- and 6-month follow-up. < 70% of both primary outcome measures are not completed. < 60% of all activities in intervention will be accomplished. < 60% of participants who complete the intervention consider the overall intervention to be acceptable.

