#### Outcome measures

All participants will be assessed for anxiety using the HADS-anxiety subscale [33] and Hamilton Anxiety Rating Scale (HAM-A; [32]). Reductions on these measures would be the expected primary outcomes of a full RCT. Prior to randomisation, measures will also be collected on depression (HADS-D; [33]), irritability (Snaith Irritability Scale; [34]), quality of life (HD-QoL; [35]), and functional ability (UHDRS TFC; [29]). The putative process or mechanism measures are the HD Concerns Questionnaire [36], a measure of coping (the brief COPE; [37]), and a psychological flexibility questionnaire (AAQ; [38]).

Participants will be asked to complete the questionnaires at baseline, within two weeks after the intervention has finished and at 3-month and 6-month follow-ups post-intervention.

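### The red-light rule for outcome completion is inverted by a double negative: as worded, completion above 30% on both anxiety measures means definite stop

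*Protocol article*

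**What the plan says.** The progression criteria are in the Protocol article, Feasibility outcomes, under Secondary outcome measures. Five quantities are graded red, amber or green: consent, retention, completion of the primary outcome measures, intervention activities and acceptability.

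For completion, the three bands are:

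- **Green:** a threshold of at least "90% of at least one primary outcome measure is completed, including 6-month follow-up".
- **Amber:** "70–89% of at least one primary outcome measure completed".
- **Red:** a less-than sign followed by "70% of both primary outcome measures are not completed".

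The measures concerned are the HADS-A and the HAM-A. The Outcome measures section says of them: "Reductions on these measures would be the expected primary outcomes of a full RCT".

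The other four red criteria put the less-than sign before a share that was achieved. For adherence, for example, red is less than "60% of all activities in intervention will be accomplished". Only the completion criterion puts it before a share that was not achieved.

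**The concern.** A less-than sign in front of a non-completion percentage describes good completion. The definite-stop rule therefore catches results that the green and amber rules pass, and it misses the results that it exists to catch.

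Deciding whether the criteria for a definitive trial are met is a listed objective under Aims, and these bands are the stated basis for that decision. A prespecified stop/go rule should give one answer without interpretation after the data are seen. Here the literal rule gives two conflicting colours when completion is good and none when it is very poor. Anyone who checks the progression decision against the published text would have to set that text aside for this criterion.

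**Working it through.** The plan has no figure to reproduce on this point. The check is to apply the three rules as worded.

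**Inputs**

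- Green: completion of 90% or more on at least one measure (Secondary outcome measures).
- Amber: completion of 70–89% on at least one measure (same section), taken here as 70% up to but not including 90%.
- Red as worded: non-completion below 70% on both measures (same section). *Both* is taken to mean that each measure meets the condition, as the counterpart of *at least one*.
- Number of participants: 30, from the recruitment target of 15 per arm (Participants, eligibility, recruitment and consent). It serves only as an illustrative denominator.

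**Step 1: translate the red rule.** Non-completion = 100% − completion. Non-completion < 70% therefore means completion > 30%.

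- Completion 100% on both: non-completion 0%, below 70%, so red. Also green.
- Completion 95% on both: non-completion 5%, so red. Also green.
- Completion 10% on both: non-completion 90%, so not red. Not green or amber either.

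**Step 2: equal completion on both measures, out of 30**

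| Completers | Completion | Colour as worded | Colour with *not* deleted |
|---|---|---|---|
| 27–30 | 90–100% | green and red | green |
| 21–26 | 70–86.7% | amber and red | amber |
| 10–20 | 33.3–66.7% | red | red |
| 0–9 | 0–30% | none | red |

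**Step 3: let the two measures differ.** Each measure can have 0 to 30 completers, which gives 31 × 31 = 961 combinations. These are counts of possible results, not probabilities.

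As worded:

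- Green or amber is met in 520 combinations: 961 − 21 × 21 = 961 − 441, because 0–20 completers on both is the only way to miss both bands.
- Of those 520, 320 also meet red (104 green and red, 168 amber and red, 48 all three). The other 520 − 320 = 200 do not, because one measure has completion of 30% or less.
- Red alone is met in 11 × 11 = 121 combinations (10–20 completers on both).
- No criterion is met in 441 − 121 = 320 combinations.

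With *not* deleted:

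- Red is met in exactly the 441 combinations in which both measures are below 70%.
- Red overlaps green or amber in none, and no combination is left without a colour.

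**The case against.** The strongest reply is that nobody would apply the sentence literally. Green starts at 90% and amber covers 70–89%, so completion below 70% is the only band left for red. The other four red criteria all treat a low achieved share as the reason to stop. The Data analysis section adds that the progression assessment will also draw on the qualitative feedback, so the decision is not mechanical. The study is a descriptive feasibility trial of 30 people, and the sentence affects no estimate and no sample size. All of this stands. It reduces the practical risk, but it does not make the sentence correct.

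A reader might also infer three stronger points, which the document does not support.

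- **Every green or amber result is also red.** This holds only when completion exceeds 30% on both measures. With one measure at 95% and the other at 10%, green is met and red is not, because the second measure has 90% non-completion.
- **The move from *at least one* measure in green and amber to *both* in red is a second error.** It is not. The opposite of at least one measure reaching 70% is both falling below 70%, so *both* is the right word.
- **The completion and retention criteria contradict each other.** With 21 of 30 retained (70%, the green floor for "retention of consented participants in both arms of the trial at 3- and 6-month follow-up"), completion at 6 months among all 30 could be at most 21/30 = 70%, which is amber. But the all-randomised denominator is an assumption, and 70% is a minimum: with 27 of 30 retained, both criteria can be green. Two criteria with different thresholds do not conflict, and a condensed article may leave the denominator to the full protocol.

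**Conclusion.** The point holds in a narrow form. The completion criterion for definite stop is inverted as worded and conflicts with the green and amber bands in the same section. At equal completion on both measures, every result of 70% or more carries two conflicting colours, and every result of 30% or less carries none. Only the range between those limits is graded as evidently intended.

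The 30% cut-off follows from the wording alone. The participant counts rest on the illustrative denominator of 30, and the 961 combinations on reading *both* as each measure separately.

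The likely explanation is a double negative in drafting, and the intended rule can be recovered from its neighbours. The document therefore does not show that the team would stop a successful study or continue a failed one. What it shows is a wrong prespecified decision threshold, which should be corrected before the progression decision is made.

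**What to change.** Delete *not* from the red completion criterion and name the measures, so that it reads: *< 70% completed on both primary outcome measures (HADS-A and HAM-A)*. Keep *both*.

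The cost is one sentence in the progression criteria, with no effect on data collection, participants or analysis.

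This edit leaves one separate, minor matter untouched. When one measure is at 90% or more and the other at 70–89%, green and amber both apply (48 of the 961 combinations), because each band asks for at least one measure. That overlap does not involve red and is not part of this point.

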#### Outcome measures

All participants will be assessed for anxiety using the HADS-anxiety subscale [33] and Hamilton Anxiety Rating Scale (HAM-A; [32]). Reductions on these measures would be the expected primary outcomes of a full RCT. Prior to randomisation, measures will also be collected on depression (HADS-D; [33]), irritability (Snaith Irritability Scale; [34]), quality of life (HD-QoL; [35]), and functional ability (UHDRS TFC; [29]). The putative process or mechanism measures are the HD Concerns Questionnaire [36], a measure of coping (the brief COPE; [37]), and a psychological flexibility questionnaire (AAQ; [38]).

Participants will be asked to complete the questionnaires at baseline, within two weeks after the intervention has finished and at 3-month and 6-month follow-ups post-intervention.

#### Randomisation and blinding

Following baseline measures being undertaken, the research team at Leicestershire Partnership NHS Trust (LPT, who have responsibility for screening and undertaking eligibility assessments and outcome measures and delivering the intervention) will email members of the research team at Lancaster University to inform them that a new recruit needs to be randomised. The LPT team will inform Lancaster University staff whether the new recruit is premanifest or manifest (i.e., whether or not they report motor symptoms consistent with a clinical diagnosis of HD during the baseline demographic questionnaire, coupled with observations by the researcher of any obvious signs of HD movements). Staff at Lancaster University will then undertake a stratified randomisation process using an automated online randomisation system (www.randomization.com), with participants allocated to either the intervention arm or TAU. The stratification for this randomisation is to ensure that those categorised as “premanifest” or “manifest” HD participants are distributed equally across both groups. Block randomisation will be carried out to ensure the control/intervention groups are relatively balanced, with random block sizes of two, with some four, due to the relatively small sample size. The block randomisation design was chosen so the research team are unaware of the next allocation given that the allocation could be from a block of two or a block of four.

Since the senior research associate is undertaking the post-intervention acceptability ratings and qualitative interviews for the intervention group, as well as the repeated outcome measures, blind assessment will not be possible. The research team at Lancaster University are blinded, at the point of randomisation, to the eligibility and baseline measures results.

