On contact with the research team, the participant will be given a further verbal description of the study and have any questions answered. If the participant agrees to go ahead, a face-to-face appointment to take written consent will then be arranged. As part of the consent process, participants will be informed that they are free to discontinue their involvement in the study at any point. Currently, the authors are also pursuing the option of adding remote verbal consent to the study by utilising videoconferencing recording, which will be subject to agreement by the NHS ethics committee. Following consent, potential participants with HD will initially be checked for basic eligibility criteria. If a person meets those basic criteria, then consent will be taken to proceed to the next step of the project. This will involve a clinical diagnostic interview with a clinical psychologist which will be undertaken at a time convenient for the participants, to ascertain whether they meet the *Diagnostic and Statistical Manual of Mental Disorders* (DSM-V; [30]) criteria for an anxiety disorder; this is needed to establish whether full criteria for eligibility will be met. Clinically relevant information gained from this interview will also form part of the treatment formulation plan for those who are allocated to the intervention arm of the study. At this assessment point, if the threshold for an anxiety disorder is reached, then cognitive functioning will also be assessed using a brief measure (the Montreal Cognitive Assessment, MoCA; [31]). The purpose of this measure is both to characterise the sample and enable therapists to understand any difficulties so the intervention can be tailored appropriately. The clinical psychologist will also make a judgement, based on both the cognitive assessment and the interview, whether the potential participant fits the eligibility for cognitive and communication abilities necessary to proceed with the intervention.

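### Stratified random blocks of two, with some four, do not keep the recruiting team unaware of the next allocation for about half of allocations

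*Protocol article*

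**What the plan says.** Under Randomisation and blinding, the protocol article describes stratified block randomisation run by Lancaster University at the request of the LPT team. The blocks are described as "random block sizes of two, with some four, due to the relatively small sample size". The purpose is stated outright: "The block randomisation design was chosen so the research team are unaware of the next allocation", and the reason offered is "given that the allocation could be from a block of two or a block of four".

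The same section shows who knows what. LPT is responsible for screening, eligibility assessment, outcome measurement and delivery of the intervention. It also supplies the stratum: "The LPT team will inform Lancaster University staff whether the new recruit is premanifest or manifest". That label rests on the participant's report of motor symptoms together with the researcher's observation. Outcome assessment is open: "blind assessment will not be possible". Under Procedure, eligibility depends in part on discretion: "The clinical psychologist will also make a judgement, based on both the cognitive assessment and the interview".

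Under Participants, eligibility, recruitment and consent, the target is 30 participants, 15 per arm, set above a working minimum of 12 per group to allow for attrition.

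**The concern.** Not knowing whether a block holds two or four places does not hide the next allocation. In a block of two, the first allocation fixes the second. In a block of four, the second allocation goes to the opposite arm with probability 2/3. Whichever block is running, the arm that is behind in the stratum is the better bet, and with such short blocks it is usually right.

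Foreknowledge could act through three steps in LPT's hands: the premanifest/manifest label in a borderline case, the timing of the randomisation request and, less directly, the eligibility judgement. What is at stake is the comparability of the two arms. Per-arm retention depends on it (the progression criteria apply to both arms), and so does any between-arm estimate carried into the full trial. Aims lists information for the sample size of a full RCT, and Data analysis includes potential clinical effectiveness and putative mechanisms.

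**Working it through.** The protocol gives no figure for predictability, so there is none to reproduce.

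**Inputs from the protocol article.** Block sizes 2 and 4; two strata; 1:1 allocation; 30 participants.

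**Assumptions.** The mix of block sizes is not stated. Let q be the share of blocks of size two. "random block sizes of two, with some four, due to the relatively small sample size" suggests q of at least 0.5, so I take 0.5 to 0.9. The split between strata is not stated either, so I take 15/15, 20/10 and 25/5. LPT is assumed to know the block sizes, which the article prints, and to keep a tally by stratum.

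**Guessing rule.** Guess the arm that is behind in the stratum; toss a coin when the arms are level.

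**Exact calculation for complete blocks.**
- Block of two: the arms are unequal before 1 of 2 places, and the guess is always right.
- Block of four: the sequences are AABB, ABAB, ABBA and their mirror images. The arms are unequal before 3, 2 and 2 places, a mean of 7/3. The guess is right twice in each sequence, so accuracy is 2 ÷ 7/3 = 85.7%.
- Share of allocations made with arms unequal = [q + (1−q)·7/3] / [2q + 4(1−q)].
- Accuracy at those allocations = [q + 2(1−q)] / [q + (1−q)·7/3].
- Correct over all allocations = share × accuracy + (1 − share)/2.

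| q | Arms unequal | Accuracy then | Correct overall |
|---|---|---|---|
| 0 (all fours) | 58.3% | 85.7% | 70.8% |
| 0.5 | 1.667/3 = 55.6% | 1.5/1.667 = 90.0% | 72.2% |
| 0.75 | 1.333/2.5 = 53.3% | 1.25/1.333 = 93.8% | 73.3% |
| 0.9 | 1.133/2.2 = 51.5% | 1.1/1.133 = 97.1% | 74.2% |
| 1 (all twos) | 50% | 100% | 75% |

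**Simulation of the actual trial** (20,000 trials of 30 participants, incomplete last blocks included, q from 0.5 to 0.9, all three splits): arms unequal at 48-55% of allocations, about 14 to 17 of 30; guess right 90-97% of the time; 71-74% correct overall. When a stratum stands two apart, only a block of four can have produced it, and the next allocation is certain.

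**If only the overall tally is known:** the arms are unequal at about 65% of allocations, and the guess is then right about 74-76% of the time (q of 0.5 and 0.75).

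**The label as a route.** With two equal strata, the strata lean towards opposite arms at about 13-15% of allocations. At those points the label given to a borderline participant decides which arm is the likely one.

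**Alternatives under the same rule** (20,000 trials each, same splits):

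| Scheme in each stratum | Correct overall | Trials with an arm of 13 or fewer | Largest arm difference |
|---|---|---|---|
| Blocks of 2 and 4 (q 0.5-0.9) | 71-74% | under 1% | 17 v 13 |
| Random blocks of 4, 6, 8 | 66-67% | about 4-5% | 18 v 12 seen, in about 0.1% |
| Big-stick, limit 2 | 61-62% | about 13% for a 20/10 split; none when both strata are odd | 17 v 13 |
| Big-stick, limit 3 | 56-57% | about 23-28% | 18 v 12 |

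**The case against.** The strongest objection is that this is a feasibility trial of 30 people with descriptive analysis. The progression criteria are percentages for consent, retention, completion of measures, adherence and acceptability, with no between-arm contrast among them. That stands, and it limits the severity.

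A reader might infer that predictability biases the recruitment rate. The documents do not support this: Primary outcome measures defines it as the share of eligible people who consent, one pooled figure not split by arm.

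A reader might also infer that concealment fails altogether. It does not. When the arms in a stratum are level, roughly half the time, the next allocation remains 50:50.

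The route to bias is narrower than the accuracy figures alone suggest. Interview, cognitive assessment, eligibility judgement and baseline measures all come before the request to Lancaster, and others in the same stratum may be randomised in between. The tally when eligibility is judged need not be the tally at allocation. This weakens the eligibility route but leaves the label and the timing of the request.

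The article gives LPT its functions as a team. It does not say that any one person keeps a tally by stratum, so the 90-97% is conditional on that. Nor does anything suggest that staff would exploit the pattern.

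Finally, short blocks were chosen because the sample is small, and every alternative gives up some balance. That is a genuine trade-off, and the cost belongs with the fix.

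**Conclusion.** The concealment statement is wrong as written for about half of allocations. With a tally by stratum and 50-90% of blocks of size two, both assumed, the arm that is behind is the correct guess 90-97% of the time at those allocations. Over all allocations 71-74% are guessed correctly, against 50% under full concealment. The result does not hinge on the mix: blocks of four alone would still give about 86%. With only an overall tally, it weakens to about 74-76% on about 65% of allocations.

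The consequence is a threat to arm comparability, and so to per-arm retention and between-arm estimates taken forward. Nothing in the documents shows that a progression criterion would change colour because of it. I rate this as something that should be fixed, not as a fault that invalidates the feasibility objectives.

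**What to change.** For allocations not yet made, replace the list within each stratum with a big-stick list: a fair coin unless the arms differ by the maximum tolerated imbalance, in which case the arm that is behind is assigned. Use a limit of 2 or 3. The minimum change is random blocks of 4, 6 and 8. Lancaster already runs the randomisation; it should hold the new scheme and not disclose its details to LPT. The premanifest/manifest label should be recorded irrevocably before the request is sent.

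The work is small: a new list and one procedural rule. The real cost is imbalance. Limit 3 conceals best but can end at 18 v 12, and an arm of 12 leaves no margin for attrition above the planned 12 per group. Limit 2 caps the difference at 17 v 13 with about 61% correct guesses, a reasonable compromise here. Blocks of 4, 6 and 8 keep sizes closer but improve guessing by only about five to eight percentage points.

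If allocation is already complete, correct the concealment statement under Randomisation and blinding, report the limitation with the results, and do not carry the scheme into the full RCT.
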